## Abstract

**Background:**

Restorative home care services help older people maximise their independence using a multi-dimensional approach. They usually include an exercise program designed to improve the older person’s strength, balance and function. The types of programs currently offered require allocation of time during the day to complete specific exercises. This is not how the majority of home care clients prefer to be active and may be one of the reasons that few older people do the exercises regularly and continue the exercises post discharge.

This paper describes the study protocol to test whether a Lifestyle Functional Exercise (LiFE) program: 1) is undertaken more often; 2) is more likely to be continued over the longer term; and, 3) will result in greater functional gains compared to a standard exercise program for older people receiving a restorative home care service.

**Methods/Design:**

Design: A pragmatic randomised controlled trial (RCT) design was employed with two study arms: LiFE program (intervention) and the current exercise program (control).

Setting: Silver Chain, a health and community care organisation in Perth, Western Australia.

Participants: One hundred and fifty restorative home care clients, aged 65 years and older.

Measurements: The primary outcome is a composite measure incorporating balance, strength and mobility. Other outcome measures include: physical functioning, falls efficacy, and levels of disability and functioning.

**Discussion:**

If LiFE is more effective than the current exercise program, the evidence will be presented to the service management accompanied by the recommendation that it be adopted as the generic exercise program to be used within the restorative home care service.

**Trial registration:**

Australian and New Zealand Clinical Trials Registry ACTRN12611000788976.

## Background

As people age there is a tendency to reduce the amount and intensity of physical activity, which can lead to a loss of strength, endurance and balance [1,2]. Such loss of function can then lead to difficulty with everyday living activities and a need for assistance for the older person to remain living in their home. Home care services usually provide this assistance by performing the activity for the older person rather than working with them to assist them to implement strategies that will maximise their function and regain the ability to undertake tasks independently.

In contrast, restorative home care services work with the older person to help them maximise their independence. They do this by incorporating a number of components such as task analysis and redesign, the use of assistive equipment and physical activity programs to improve function, into a short term goal-oriented service [3-5]. In general, restorative home care services provide a “traditional” exercise program, aimed at improving strength and balance to help prevent falls and improve function for the older person. These programs require the older person to complete a set number of exercises, a number of times per day or a number of times per week. The person often completes them for a short period or sporadically, however when they feel they are “better” or have improved their function they often stop.

Recent research has found older people receiving a home care service describe their preferred physical activity as being incidental, such as cleaning the house, walking to the shops and doing the gardening, rather than attending exercise classes or playing sport, which is often preferred by younger generations [6]. Given this and the success of the Lifestyle Functional Exercise (LiFE) program in improving physical function and reducing falls among older people living in the community [7], it was considered important to conduct an RCT to test whether it might be more effective than a traditional exercise program when incorporated into a restorative home care service.

Prior to embarking on the RCT it was necessary to determine whether LiFE was suitable for older restorative home care clients. A pilot study was therefore conducted and LiFE was found to be appropriate for this population [8].

This paper describes the study protocol of the pragmatic randomised controlled trial which compared the effectiveness of LiFE, in both the short and long term, and the current traditional exercise program used in a restorative home care service. It is hypothesised that the LiFE intervention compared to the current exercise program will: 1) be undertaken more often; 2) be more likely to be continued over the longer term; and, 3) result in greater functional gains.

This trial is pragmatic in several aspects including the implementation of the trial within the current restorative home care services of a health and community care organisation in Western Australia. Pragmatic trials are of increasing interest to government health bodies including the National Institute of Health (NIH) and Australia’s Department of Health and Ageing [9], as they provide “real life” results rather than “ideal setting” results often not transferrable to health services.

## Methods

### Study design

This study was a pragmatic, non-blinded, parallel arm randomised controlled trial testing the effectiveness of the LiFE program compared to the current traditional exercise program when delivered within a restorative home care service.

### Participants and setting

The study participants comprised older persons living in Perth suburbs who were referred for a restorative home care service and who met the RCT inclusion criteria. These criteria were: over 65 years of age; assessed by their Care Manager as needing a physical activity program; not having a diagnosis of dementia or other progressive neurological disorders; and, being able to communicate in English.

Silver Chain is an Australian health and community care organisation that delivers a myriad of services, including restorative home care services. The restorative home care services are delivered by an interdisciplinary team consisting of physiotherapists, occupational therapists and registered nurses acting as Care Managers, assisted by aides to provide any direct care needed. Silver Chain delivers two restorative home care services to their older clients; the Home Independence Program (HIP) and the Personal Enablement Program (PEP). HIP is delivered to older people living in the community who need short term assistance to regain their independence, while PEP is delivered to older people who have been in hospital and need the short term service on discharge to help them return to living independently.

HIP and PEP restorative home care services comprise a number of components, including: the promotion of active engagement in daily living activities through work simplification and assistive technology; an exercise program to improve strength, balance and endurance; chronic disease self-management; falls prevention strategies; improvement and maintenance of skin integrity; and medication, continence and nutrition management [10]. HIP is generally delivered for a maximum of 12 weeks and PEP 8 weeks. It was expected that the majority of older people who would be involved in this RCT would be PEP clients, referred after hospital discharge because their referral numbers are higher than HIP.

### Sample size

The sample size was calculated based on 80% power, a 5% significance level and a ‘medium’ effect size of 0.5 [11] related to the two groups, using as the primary outcome, a composite measure incorporating balance, strength and mobility. This effect size was considered sufficient to recommend a change in practice, given that functional improvement is also expected in the current practice group. Based on Peat [12] a sample size of 64 in each group is indicated. Allowing for a 12% drop out rate as found during the pilot study [8], approximately 75 participants in each group were needed, or 150 in total.

### Recruitment, randomisation and allocation concealment

When a client met the eligibility criteria, and agreed that an exercise program would help them achieve their service goals, the Care Manager gave the client: a brief explanation of the study; an introductory letter addressed from the researcher; an information sheet and consent form; and, asked if the researcher could contact them to discuss the project further. If the client agreed, the Care Manager informed the researcher, who called the client within three days to answer any questions and set up a time to visit, gain written consent and complete the baseline data collection. After baseline data were collected, clients were randomised to the intervention or control groups. Notification of group assignment was provided by the researcher to the Care Managers either through email or their computerised phone system and delivery of the allocated exercise program was commenced at the Care Manager’s next visit to that client.

The randomisation process was conducted by a Senior Researcher not involved in the study. Study numbers were randomly allocated to group (‘LiFE’ or ‘current’) using the (simple) random number generator in STATA version 10. Slips of paper with study number and group allocation were then placed in envelopes of the same colour as the paper slip to avoid any tampering with the randomisation. Before sealing the envelopes the study numbers were written on the outside, they were put in sequential order and given to the researcher conducting the trial. The researcher involved in collecting follow up data was not blinded to group allocation.

### Exercise programs

#### Lifestyle and Functional Exercise (LiFE) Program (Intervention)

The LiFE program was developed to improve balance and increase strength in older community dwelling people by embedding exercise into everyday activities [7]. Seven of the exercises in the program are for balance and six are for lower limb strength. It was initially developed as a falls prevention exercise program [13] however there were other outcomes in terms of increased participation and functional improvements that indicate it would be appropriate for our population of restorative home care clients.

After a client had been assessed as needing an exercise program and agreed to participate in the RCT and was randomised to LiFE, the LiFE program was explained and the different exercises described during the Care Manager’s next visit. How these exercises were incorporated into their daily routines, and which they would start with, were discussed and agreed with the older person. The client was also given a manual explaining each of the exercises. Follow up visits were used to monitor how the client was going with the first agreed exercises and to encourage the client to start doing others. In Clemson et al’s original study, LiFE was delivered over five sessions, with two follow up sessions and two phone calls over a six month period [7]. However, in this RCT, clients were expected to be seen every ten to fourteen days by their Care Manager (average three visits), and LiFE was just one aspect of their service that would be discussed during these visits.

#### Current exercise program (Control)

The current exercise program is based on the Otago exercise program developed by Campbell and Robertson [14] which was also initially developed as a falls prevention exercise program. The Otago program has been modified over time by the team delivering restorative home care services, in response to client preferences, to not include weights and, depending on the client’s requirements, sometimes included additional exercises.

After giving written consent and completing baseline data collection, participants allocated to the current exercise program were given a one page instruction sheet (back and front) illustrating the exercises (picture), number of times per day and number of days per week to complete them. The Care Managers explained the exercises they prescribed and during follow up visits they discussed and/or supervised the clients completing new exercises. Based on the Care Managers’ description of “usual” practice, it was expected that an average of three visits involving discussions about their exercises would be included.

Depending on group allocation, Care Managers took a LiFE manual or the current exercise program sheet, plus a calendar, to each client at the first visit after randomisation. The clients were asked to tick each day on the calendar they completed the exercises and to keep this until their six month follow up visit. A summary of the study schemata is presented as Figure 1.

**Figure 1 F1:**
[figure not shown]
Study schemata.

#### Data to be collected

All data were collected in the participants’ homes and both activity programs were undertaken either in the participant’s home or different places they may have visited during their week, such as: a shop, park, or footpaths. No specific equipment was needed for either program.

Demographic, home care service and falls information as well as functional data were collected for participants in both the intervention and control groups at baseline, eight weeks and six month follow-up. The six month follow-up occurred four months after the Care Manager ceased the restorative home service with the client. Table 1 provides a basic description of each of the outcome measures that were used in this study.

**Table 1 T1:** Outcome measures and instruments

**Instrument**	**Reference**	**Measures**	**Validity and reliability reported**
Functional Reach	[15]	Balance	Yes
Falls Efficacy Scale	[16]	Fear of falling when completing daily tasks	Yes
Sit-to-stand 1 and 5 times	[17]	Lower body strength and balance	Yes
Timed Up and Go	[18]	Functional mobility	Yes
10-item Vitality Plus Scale	[19]	Potential health-related benefits of exercising	Yes
Tandem walk	[20]	Dynamic balance	Yes
ABC Scale	[21]	Confidence (falls) in completing more challenging tasks	Yes
LLFDI	[22]	Levels of disability	Yes
Disability Component			
LLFDI	[23]	Lower and upper body function	Yes
Function Total			

*Note*. ABC scale is the Activities Specific Balance Confidence Scale, LLFDI the Late Life Function and Disability Instrument.

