### Data analysis

Data will be analysed using the Statistical Package for the Social Sciences computer statistical software, version 19 [24]. Both *intention-to-treat* (ITT) and *per protocol* (PP) analyses will be performed. For each outcome measure, we will calculate the change that has occurred during the intervention period by subtracting the baseline from the 8-week values. Where the distribution of the change is approximately normal, an independent *t*-test will be used to compare the groups. When the data are not normally distributed a Mann-Witney U test will be used. Categorical data will be analysed using a Chi-square test.

The summary variable to be used as the primary outcome measure will be created using clients’ functional reach, chair sit to stand, timed up and go and tandem walk scores. A factor analysis will be carried out to identify the relative importance of these four variables in the dataset, at baseline. This analysis will produce a set of factor loadings or ‘weights’ that can then be used to construct the new summary variable (as a weighted linear combination of the four separate measures above). The weights will be scaled so that, at baseline, the mean of the summary variable is zero and its standard deviation is 1. The same linear combination will be applied to create the summary variable at 8-weeks. Any change in the summary variable over the 8-week period will be assessed for statistical significance in exactly the same manner as the other outcome variables (as described above).

Analyses of the post-testing results at 6 months will consist of a regression model for the outcome of interest, adjusting for the correlations due to the multiple measurements on each individual by treating the person ID as a random effect. Multiple linear regressions will be used to identify any differences between the groups at initial data collection, eight weeks and six months, and to examine differences between the groups in terms of change in measures over the follow up period. A p value of <0.05 will be considered statistically significant. Data analysis will be supervised by a statistician who is not involved in conducting the trial.

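### The four-month off-service gap and the 8-week intervention period fit only a service of about 8 weeks, but HIP may run to 12, and the primary test leaves service type unused

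*Protocol article*

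**What the plan says.** The trial takes clients from two services. Under Participants and setting, the article says that "HIP is generally delivered for a maximum of 12 weeks and PEP 8 weeks". HIP serves people living in the community and PEP serves people leaving hospital. On the mix, "It was expected that the majority of older people who would be involved in this RCT would be PEP clients"; no HIP share is given.

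Under Data to be collected, measurements are taken "at baseline, eight weeks and six month follow-up", and "The six month follow-up occurred four months after the Care Manager ceased the restorative home service with the client". Outcome measures adds that each person's study lasted six months. It justifies the six-month visit on the ground that programmes often lapse once the Care Manager no longer prompts the client.

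Under Data analysis, for each outcome, "we will calculate the change that has occurred during the intervention period by subtracting the baseline from the 8-week values". The groups are then compared by an independent t-test, or by a Mann-Whitney test if the change is not normally distributed. The primary composite is tested in the same way. The later regressions name a random effect for person and no other covariate.

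Allocation was made "using the (simple) random number generator in STATA version 10", with no stratification described.

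**The concern.** Six months less four leaves about two months of service. The four-month statement and the 8-week intervention period therefore both assume a service of about 8 weeks, which the article's own description of HIP does not guarantee.

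Two results depend on this. The primary outcome is the 8-week change: for a client still in service at week 8 it describes mid-service status, while for others it describes status at or after the end of service. The second hypothesis is that LiFE is more likely to be continued over the longer term, and the article ties that to the period without a Care Manager. If the time off service differs between clients, a single figure of four months misdescribes what was tested.

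Service type also marks two populations that plausibly recover differently, and it is known before randomisation. The primary test, as fixed in the text, does not use it.

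**Working it through.** **Inputs.** Maximum service D: 12 weeks (HIP) and 8 weeks (PEP), from Participants and setting. Visits at 8 weeks and six months, and the stated gap of 4 months, from Data to be collected. Total N = 150, 64 per group before dropout and target effect 0.5 SD, from Sample size. Six months is taken as 26 weeks and one month as 4.35 weeks.

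**Step 1: the plan's own figure.** With baseline at service start, the gap is 26 − D. For D = 8: 26 − 8 = 18 weeks, and 18/4.35 = 4.1 months. The stated four months is reproduced for an 8-week service.

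**Step 2: HIP at its maximum.** For D = 12: 26 − 12 = 14 weeks, and 14/4.35 = 3.2 months. At the 8-week visit, 8/12 = 67% of the service has been delivered and 4 weeks (33%) remain.

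**Step 3: the other anchoring.** If the last visit really came four months after a 12-week service, it would fall at 12/4.35 + 4 = 6.8 months. That conflicts with the six-month study duration under Outcome measures.

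**Step 4: service that began before baseline.** Let L be the weeks of service before baseline (not stated; assumed 0 to 2). The gap is 26 − (D − L), and the share of a 12-week service delivered by the 8-week visit is (8 + L)/12.

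| L (weeks) | Share of a 12-week service delivered at the 8-week visit | Gap at six months, D = 12 | Gap at six months, D = 8 |
|---|---|---|---|
| 0 | 67% | 14 wk (3.2 mo) | 18 wk (4.1 mo) |
| 1 | 75% | 15 wk (3.4 mo) | 19 wk (4.4 mo) |
| 2 | 83% | 16 wk (3.7 mo) | 20 wk (4.6 mo) |

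For any common L, the two service lengths stay 4 weeks apart, so one figure cannot describe both.

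**Step 5: chance imbalance in service type.** If 30 of 150 clients are HIP (assumed), the number in one arm is Binomial(30, 0.5), with a 95% range of 10 to 20. With about 75 per arm, the 95% range of the between-arm difference in HIP share s is ±1.96 × √[s(1 − s) × 2/75]. This gives ±10 points at s = 10%, ±13 at 20%, ±15 at 30% and ±16 at 49%.

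**Step 6: what that could do to the estimate.** At the edge of the range, a 20/10 split, the shares differ by 20/75 − 10/75 = 0.133. If HIP and PEP differ in mean change by 0.25 to 1.0 SD (assumed), the estimate moves by 0.133 × 0.25 = 0.03 SD to 0.133 × 1.0 = 0.13 SD. For comparison, the standard error at 64 per group is √(2/64) = 0.18 SD, and the target effect is 0.5 SD.

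**Step 7: precision.** Service type explains about s(1 − s)δ² of the variance of the change, where δ is the HIP–PEP difference in SD units. At s = 0.2 and δ = 0.5: 0.2 × 0.8 × 0.25 = 0.04, or 4%. At δ = 0.25 it is 1%, and at δ = 1.0 it is 16%.

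**The case against.** The best defence is that this is one loosely worded sentence. Twelve weeks is a general maximum, no distribution of durations is given, and HIP is expected to be the minority. That stands, and it limits the point to HIP clients served beyond about 8 weeks. Some service may also precede baseline, because the Care Manager already knows the client before consent and "delivery of the allocated exercise program was commenced at the Care Manager’s next visit to that client". That stands too, and step 4 shows how far it softens the figures. The schedule, with the six-month study duration, already suggests visits timed from baseline; the proposed wording makes that explicit.

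A reader might go further in four ways that the documents do not support.

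- **That the article calls week 8 the end of the intervention.** It does not. It calculates change over an intervention period from baseline to 8 weeks, and an end at week 8 is only an inference.
- **That the visit schedule is also contradictory.** For LiFE, "clients were expected to be seen every ten to fourteen days by their Care Manager (average three visits". An average number of visits does not contradict a maximum duration, and the control section counts only visits that involve discussion of the exercises. If three visits is typical, exercise delivery may often finish before week 8 even where the wider service continues.
- **That the arm comparison is biased.** Both arms have the same visit times and, in expectation, the same HIP/PEP mix. Simple randomisation with an unadjusted test is valid, and its standard error already allows for chance imbalance.
- **That the remaining envelopes should be prepared separately by service.** That would change the randomisation mid-trial in a study whose recruitment is described in the past tense. Covariate adjustment serves the purpose without it.

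Covariates for the six-month regressions may properly sit in an analysis plan that is not shown. The primary test is different, because the article fixes it as an unadjusted comparison.

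**Conclusion.** The concern holds in a limited form. The unqualified four-month statement and the 8-week intervention period conflict with a HIP service that may run to 12 weeks. At that maximum, with baseline at service start, up to a third of the service remains at the primary visit. The six-month visit then comes about 3.2 months after service, against about 4.1 months for an 8-week service; one or two weeks of service before baseline would make the 3.2 into 3.4 to 3.7.

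The consequence is descriptive: it changes what the 8-week and maintenance results mean for a minority of unknown size. It does not threaten the validity of the comparison or alter the sample size.

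Adjusting for service type is an improvement, not the repair of an error. Under the assumed 30 HIP clients and a 0.5 SD difference between services, it removes about 4% of the variance and guards against a shift of about 0.07 SD (0.133 × 0.5) at the edge of the chance range. Both figures depend on a HIP share and a HIP–PEP difference that the documents do not give.

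**What to change.** 1. State that both follow-up visits are timed from baseline, at 8 weeks and six months.
2. Reconcile the four-month wording (Data to be collected) and the intervention-period wording (Data analysis) with the service durations under Participants and setting, or remove them. The 8-week result can be described as change at a fixed assessment time.
3. Record each client's actual service-end date and report time off service at six months by arm. Keep this descriptive: it arises after randomisation and should not be an adjustment variable.
4. Replace the unadjusted primary test with a linear model for the 8-week change, with arm and service type (HIP/PEP) as terms. Include service type in the six-month model as well.

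The cost is negligible: some wording, one date per client, and one baseline covariate known for everyone before randomisation. The analysis is written in the future tense, so the change can be fixed before the data are analysed. The sample size stays as it is.
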